### Randomization

After the baseline assessment has been completed, participants will be randomly allocated to the home based exercise intervention or the control group (Figure 1). A computer generated random numbers table will be used, and a paper with the group number will be folded and concealed in numbered opaque envelopes by an independent staff member who is not part of the research team**.** Following the baseline assessment, the next consecutive envelope will be opened by a researcher not involved in the assessments, and the group allocation will be conveyed to the researcher implementing the intervention activities. To avoid any potential sampling contamination, any couples enrolled in the study will be randomized into the same group [31]. The participant will be informed as to which group they are allocated, and for those in the intervention group, an appointment will be made at the assessment laboratory for provision of the home exercise program.

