### Statistical analysis

Baseline and post intervention measures will be reported as means (m) ± standard deviations (SD). Data will be analysed on an intention to treat basis. Change in the selected primary outcome measure and secondary outcomes will be evaluated using two way Repeated Measures ANOVA to determine group main effect, time main effect, and interaction effect between group and time. Level of significance will be set at P < 0.05. Participants in the exercise intervention group will be grouped according to high adherence (> median adherence for the full group) and low adherence (≤ median adherence level). Repeated measures ANOVA will be used to determine whether there is a difference in change in the primary and secondary balance measures between the high adherence and low adherence group.

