### Sample size

Power analysis was performed for the primary outcome measure (Step Quick Turn test on the Neurocom® Balance Master), using the mean score for the Step Quick Turn test (sway-degrees/s) results from a previous exercise intervention trial of older people with mild balance impairments [34]. It was estimated that 34 participants per group (68 participants in total) would be required to have at least 80% power to detect a 15% improvement in the Step Quick Turn test using the turn sway measure on the Neurocom Balance Master long-plate (degrees/s), (assuming 50% standard deviation improvement with the intervention [sd = 10.2, effect size = 0.5] at P < 0.05 (two-tailed). This calculation includes allowance for an anticipated 20% dropout rate. This sample size should also be adequate for other secondary outcome measures including the Limits of Stability test (Neurocom® Balance Master), the Step Test, and Functional Reach Test.

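### Couples are allocated to the same group, but the planned ANOVA treats all participants as independent, and the envelope procedure does not say that both partners are assessed before the pair is allocated

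*Protocol article*

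**What the plan says.** The Randomization section of the protocol article sets a special rule for couples, to avoid contamination: "any couples enrolled in the study will be randomized into the same group". For everyone it describes the mechanism as "Following the baseline assessment, the next consecutive envelope will be opened by a researcher not involved in the assessments", after which "The participant will be informed as to which group they are allocated". It does not say how a couple is matched to an envelope, or in what order partners are assessed.

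The Statistical analysis section states that "Change in the selected primary outcome measure and secondary outcomes will be evaluated using two way Repeated Measures ANOVA", with tests of group, time and their interaction. The Sample size section counts individuals ("34 participants per group (68 participants in total) would be required") and allows for dropout. Couples are not mentioned in the Statistical analysis, Sample size or Missing data sections.

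**The concern.** A repeated measures ANOVA allows for correlation between the two measurements on one person. It assumes that different persons are independent. The couples rule creates clusters of two that always fall in the same arm, so any positive correlation between partners adds to the variance of the group comparison without entering the standard error. The error is in the anti-conservative direction.

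Correlation is plausible on the protocol's own terms. The couples rule exists because partners can influence each other, and the programme is done at home and includes walking, so two partners in the exercise arm may train together and share good or poor adherence.

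There is a second, procedural gap. If one partner were allocated before the other had been assessed, the couples rule would fix the second partner's arm, and the couple would know it. That could affect whether the second partner joins and how that partner performs on a turn test that depends on effort and is both an entry criterion and a primary outcome. It could also lead to the arm being revealed to an assessor who is meant to be blind.

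**Working it through.** **The plan's own figure.** The plan has no figure for clustering to reproduce. The nearest is 34 per group. With effect size 0.5, 80% power and two-sided 5%, the two-sample formula gives 2 × (1.96 + 0.84)² / 0.5² = 62.7, so 63 per group, and 63 / 0.8 = 79 with 20% dropout. The stated 34 is therefore not a two-sample figure to which a design effect has been added. Why it does not reproduce is a separate matter, and nothing below depends on it.

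**Inputs.** From the protocol: couples share an arm; 68 participants in total; 5% two-sided. Assumed, because the protocol gives neither: p, the share of participants who are in couples, and ICC, the correlation between partners' changes.

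**Design effect.** Among N participants there are pN/2 couples (m = 2) and (1 − p)N single participants (m = 1).

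- Σm² = 4 × pN/2 + (1 − p)N = N(1 + p), and Σm = N, so Σm²/Σm = 1 + p.
- DEFF = 1 + (Σm²/Σm − 1) × ICC = 1 + p × ICC.
- True error of the unadjusted 5% test = 2 × (1 − Φ(1.96 / √DEFF)).
- Effective sample = 68 / DEFF.

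| p | ICC | Couples among 68 (68p/2) | DEFF | 1.96/√DEFF | True error | Effective sample |
|---|---|---|---|---|---|---|
| 0 | any | 0 | 1.00 | 1.96 | 5.0% | 68 |
| 0.1 | 0.1 | about 3 | 1.01 | 1.950 | 5.1% | 67.3 |
| 0.3 | 0.2 | about 10 | 1.06 | 1.904 | 5.7% | 64.2 |
| 0.5 | 0.3 | 17 | 1.15 | 1.828 | 6.8% | 59.1 |
| 1 | 0.5 | 34 | 1.50 | 1.600 | 11.0% | 45.3 |

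The last row is an extreme bound, not a forecast. The table takes the same p and ICC in both arms. If the correlation came only from shared exercise, it would act in one arm, and with equal arms the inflation would be halved: at p 0.5 and ICC 0.3, 1 + 0.15/2 = 1.075, 1.96/√1.075 = 1.890, and the error is 5.9%.

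**Which correlation matters.** Write the value for person i in couple j at time t as fixed effects + c_j + s_ij + e_ijt, where c_j is a couple intercept and s_ij a person intercept. The change from baseline to 16 weeks is the time and interaction effects + (e_ij,16 − e_ij,0). Both intercepts cancel. Two results follow:

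1. Similarity between partners in stable level does not bias the interaction test. Only correlation in their changes does, so the ICC above is that of change.
2. Adding a couple random intercept to the planned model leaves partners' changes modelled as independent. A couple by time term is needed, which with two time points is the same as a couple effect in a model for change.

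**The case against.** The size of the harm rests on two inputs that the protocol does not give. Half the sample in couples means 17 couples among 68 people. To enrol as a couple, both partners must volunteer, both must fall outside age and gender limits on the turn test, and both must pass exclusions that include cardiac problems, stroke and mobility-limiting impairment. A few couples is the easier case to believe, and at p 0.1 and ICC 0.1 the error is 5.1%. A shared household argues mainly for similar levels, which cancel from the interaction, and the exercises are tailored to each person. All of this stands. A reader might infer that the standard errors are certainly too small. The documents do not support that: it requires that couples enrol and that their changes are positively correlated.

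A reader might also infer that concealment is lost for second partners, or that one envelope is used for each person. Neither is stated. The section speaks only of the next envelope in sequence, never describes partners enrolling at different times, and can be read as both being assessed before one envelope is opened. The envelope opener is not involved in assessment, assessors are blind, and entry depends on the device's norms; these limit any bias. What stands is narrower: nothing in the text prevents the other order, in which those safeguards would not hide the arm from the couple.

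Finally, a statistical analysis plan may exist and an article condenses. But the protocol itself creates the clusters and names the test, so this is a mismatch between two stated elements and not a detail left for later.

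**Conclusion.** The mismatch is certain: allocation is by couple where couples exist, while the named analysis and the sample size treat everyone as an individual. Its effect is conditional. Over the assumed range from p 0.1 with ICC 0.1 to p 0.5 with ICC 0.3, the nominal 5% test runs at about 5.1% to 6.8%. It is exactly 5% if no couples enrol, and closer to 5% than tabulated if the correlation arises in the exercise arm only. The concealment gap is an ambiguity to close, not a demonstrated breach. Severity is minor to moderate. It is still worth correcting, because the likely direction is anti-conservative and because a loss of concealment could not be repaired afterwards.

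**What to change.** **Statistical analysis.** Keep the couples rule. Test the group effect on change, or on the 16-week value adjusted for baseline, with standard errors clustered by couple (single participants as clusters of one) and a small-sample correction. Alternatively, fit a couple random effect in that same change-score or ANCOVA model, or equivalently a couple by time term in the repeated measures model. Do not rely on a couple random intercept alone. Report the number of couples in each arm.

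**Randomization.** State that both partners of a couple complete consent and baseline assessment before one envelope is opened for the pair. Dropping late-joining partners from the analysis is not needed for this correction and would have to be squared with the stated intention-to-treat basis.

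**Cost.** Wording in two sections, some scheduling so that partners are assessed before allocation, and slightly wider intervals if partners' changes are positively correlated: by a factor of √1.15 = 1.07 at p 0.5 and ICC 0.3. With very few couples the couple variance would be poorly estimated, which favours the clustered standard errors. If no couples enrol there are no clusters of two to adjust for.

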### Intervention group activity

The intervention group will participate in a tailored (individualized) home based balance exercise program, provided by a trained researcher. This exercise program is based on the Otago program, a program shown to be effective in improving general balance in older people with mild balance dysfunction [29], but will include additional exercises selected to improve impairment of turning. The exercises selected for each participant in the intervention group will be based on assessment findings of areas of impairment. Two exercises of the 6–8 exercises prescribed will be selected to improve turning ability, while the other exercises will target other aspects of balance and mobility impairment based on the assessment findings. The selection of exercise and progression level will be tailored to the level of the participant ability. An exercise sheet will be provided by the researcher to each participant with illustrations and instructions detailing how to do the exercises, and dosage. The researcher will demonstrate each of the exercises and will ask the participant to perform the exercise just after the demonstration to ensure the participant understands how to do the exercise correctly. Participants will be provided with a written copy of the exercise program, and the researcher’s contact details if they need to discuss any aspect of the exercise program between visits. The home based exercise program is expected to take 20–30 minutes per session on average, including rests. Participants will be encouraged to continue the exercise program at least four times a week for the 16 weeks. The dosage is consistent with recommendations from a meta-analysis of exercise interventions in reducing falls [14]. In addition to the balance, strengthening and mobility related exercises, participants in the intervention group will also be provided with a graduated walking program, in which they will be asked to include a walking program 3 days/week, with gradually increasing distances.

Participants in the exercise intervention will return to the assessment laboratory for three occasions in the 16 week duration (one visit after 3, 6 and 9 weeks) to review the exercise program, modify exercises if required, and motivate the participant to persist with the exercises.

Adherence to exercise programs is an important determinant of outcome. Strategies to support adherence in this study include encouragement through phone calls between visits will be done by researcher who will prescribe and monitoring the exercise intervention. Participants will complete and return an exercise diary.

### Control group activity

Following the baseline assessment and randomization, the control group will be asked to continue with their usual activities.

### Follow up data collection

Intervention group participants will be asked to complete a daily log of their exercise participation, to be used to calculate exercise adherence. Both the intervention and control group will receive four phone calls interspersed over the 16 week period (weeks 4, 8, 12 and 16) by a researcher to obtain details regarding any falls that occurred between phone contacts.

### Safety

All assessments in this study will be carried out by trained researcher. The assessment procedures include a range of physical performance assessment tests, many of which are commonly used by physiotherapists involved in assessment and treatment of older people. The Neurocom® balance assessments are not commonly used by clinicians, but have been used safely in published research [29,32]. Participants will use a safety jacket and harness during several of the Neurocom® force platform balance assessments, which will ensure they will not overbalance during the assessment force platform tests. In other tests, they will be closely supervised by the research officer conducting the assessments. The individualized home based exercise is based on the Otago home based exercise programs that have been shown in a number of studies among at risk older people to be safely implemented [32,33]. The researcher implementing the exercise intervention will have training provided by an experienced physiotherapist (KH), and will use an exercise prescription algorithm developed for the study.

### Ethical considerations

The participant information sheet includes information on the purpose of the study, and potential risk, benefits and withdrawal procedures, which will be explained to the participants prior to seeking consent to participate. All information obtained through this study will remain confidential. Participant identifying data will only be used for the purpose of research and no individual identifiable information will be used in any types of publication. All data will be recorded on paper based forms, and will then be scanned to the electronic database. Electronic files will be stored on password protected computers, with access limited to members of the research team. All written files will be stored in locked filing cabinets in the research officer’s office, and will be archived and retained for five years after publication. At the end of this period, all paper based data will be shredded and the electronically data will be erased.

Ethics Committee approval has been received from Curtin University Research Ethics Committee (Approval No. FHEC PT231/2013, Approval Date: May 30,2013) and the Universiti Putra Malaysia Ethic Committee (Approval No. IG April Curtin (13) 04, Approval Date: May 10,2013). Permission to conduct research in Malaysia has been obtained from the Economic Planning Unit (EPU), Department of Prime Minister of Malaysia.

### Primary outcome measure

The primary outcome will be the Step Quick Turn test (Neurocom® Balance Master) (a laboratory measure) (amount of sway-degrees/s) and Timed Up and Go Test (a clinical measure). Other measures of balance and mobility performance, falls efficacy, and adherence to exercise program will be considered as secondary outcomes. While falls data is being collected, the study is not powered sufficiently to identify a significant difference in falls between the two groups.

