**Methods/Design:**

A single blind randomized controlled trial will be conducted, with assessors blind to group allocation. Study participants will be aged 50 years and above, living in the community and have been identified as having impaired turning ability [outside of age and gender normal limits on the Step Quick Turn (180 degree turn) task on the Neurocom® Balance Master with long plate]. After a comprehensive baseline assessment, those classified as having balance impairment while turning will be randomized to intervention or control group. The intervention group will receive a 16 week individualized balance and strength home exercise program, based on the Otago Exercise Program with additional exercises focused on improving turning ability. Intervention group will attend four visit to the assessment centre over 16 weeks period, for provision, monitoring, modification of the exercise and encourage ongoing participation. Participants in the control group will continue with their usual activities. All participants will be re-assessed on completion of the 16 week program. Primary outcome measures will be the Step Quick Turn Test and Timed-Up and Go test. Secondary outcomes will include other clinical measures of balance, psychological aspects of falls, incidence of falls and falls risk factors.

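### Two primary outcomes share one 0.05 level with no success rule: if either can carry the trial, the false positive rate is about 7% to 9.75%, not 5%

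*Protocol article*

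**What the plan says.** The protocol article counts its primary outcomes in two ways.

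- **Two primaries.** The Abstract (Methods/Design) says "Primary outcome measures will be the Step Quick Turn Test and Timed-Up and Go test". The Primary outcome measure section names the Step Quick Turn test, with its parameter, together with the second test: "amount of sway-degrees/s) and Timed Up and Go Test (a clinical measure".
- **One primary.** The Statistical analysis section says "Change in the selected primary outcome measure and secondary outcomes will be evaluated using two way Repeated Measures ANOVA". The Sample size section says "Power analysis was performed for the primary outcome measure (Step Quick Turn test on the Neurocom® Balance Master".
- **One level for everything.** The Statistical analysis section adds "Level of significance will be set at P < 0.05". No section gives an alpha split, an order of testing, or a rule on whether one or both primaries must be significant.
- **Sizing.** The calculation claims "at least 80% power to detect a 15% improvement in the Step Quick Turn test", with the inputs "sd = 10.2, effect size = 0.5] at P < 0.05 (two-tailed", and arrives at "34 participants per group (68 participants in total". The section adds that the sample should serve the Limits of Stability, Step Test and Functional Reach outcomes. Timed Up and Go is not mentioned there.
- **Versions of Timed Up and Go.** Table 1 lists a single-task and a dual-task version. The Primary outcome measure section does not say which is meant.

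**The concern.** The document does not say what result would make this trial positive. With two declared primaries, one unadjusted level and no success rule, sway alone, Timed Up and Go alone, or only the two together could be claimed as the primary finding. The readings have different error properties. If either outcome suffices, the 5% level no longer applies to the primary conclusion. If both are needed, the error is safe, but the sample size section covers only one of the two tests that must succeed. Leaving the choice open until results are known would let it depend on which outcome happened to be significant.

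**Working it through.** **Inputs.** Two primary outcomes (Abstract; Primary outcome measure). Level 0.05 (Statistical analysis), two-sided (Sample size). Effect size 0.5 and SD 10.2, so a difference of 0.5 × 10.2 = 5.1 degrees/s; power 80% (Sample size). The correlation between the two test statistics is not given, so it is varied from 0 to 0.9 as an assumption.

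**The plan's own figure.** The plan states no familywise error rate, so there is none to reproduce. Its only related figure is 34 per group, which concerns sway alone. The plain two-group formula in step 5 does not return 34. That is a separate sample size question, and nothing here depends on it.

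**1. Either outcome suffices, independent tests.** With no effect on either outcome, the chance of at least one false positive is 1 − (1 − 0.05)² = 1 − 0.9025 = 0.0975. The upper bound under any dependence is 0.05 + 0.05 = 0.10.

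**2. Either outcome suffices, correlated tests.** For bivariate normal test statistics with correlation r, the error is 1 − P(|Z1| < 1.96 and |Z2| < 1.96):

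| r (assumed) | Either suffices | Both required |
|---|---|---|
| 0 | 9.75% | 0.25% |
| 0.3 | 9.51% | 0.49% |
| 0.5 | 9.07% | 0.93% |
| 0.7 | 8.35% | 1.65% |
| 0.8 | 7.81% | 2.19% |
| 0.9 | 7.04% | 2.96% |

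**3. Both required.** The last column is 0.05 + 0.05 minus the column before it, for example 0.10 − 0.0975 = 0.0025. It applies when neither outcome has an effect. When only one has no effect, the error is at most 5%. A both-required rule therefore never exceeds 5%.

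Its cost is power: P(both significant) cannot exceed the smaller of the two individual powers. As an illustration, take the planned 80% for sway and assume 80% for Timed Up and Go, which the article does not state. Independent tests then give 0.80 × 0.80 = 0.64 for both, and 0.80 is the ceiling.

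**4. Fixed sequence, sway then Timed Up and Go, each at 0.05.** If sway has no effect, any false claim requires rejecting sway, with chance at most 0.05. If sway has an effect and Timed Up and Go has none, a false claim requires rejecting Timed Up and Go, again at most 0.05. The familywise error is at most 5% whatever the correlation, and sway keeps the 0.05 used for sizing.

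**5. Alpha split, for comparison.** At 0.025 per outcome the familywise error is 4.94% if independent and 4.65% at r = 0.5. The price can be read from the plain two-group formula, n per group = 2(z_α + z_β)²/0.5²:

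- at 0.05: 8 × (1.960 + 0.842)² = 62.8, so 63;
- at 0.025: 8 × (2.241 + 0.842)² = 76.04, so 77.

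An equal split thus needs 77/63 = 1.22 times as many participants before dropout.

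**The case against.** The strongest defence is that no section states an either-wins rule. The Primary outcome measure section uses a singular noun and joins the two tests with *and*, so a both-must-succeed reading is open, and under it the error never exceeds 5%. This stands. A reader might infer that the trial's false positive rate simply is 10%. The text does not support that, because the figure holds only under one of two open readings and 9.75% is its upper end. Timed Up and Go itself includes walking to a line and back, so a positive correlation with a turning test is plausible and would lower the figure.

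A statistical analysis plan that is not shown could hold the decision rule, and stating a nominal 0.05 does not exclude one. This stands only in part, because the article itself fixes two primaries, one level and one sized outcome, and contradicts itself on their number.

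Three further inferences go too far:

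- The word *selected* in the Statistical analysis section might be taken as permission to choose the primary after seeing results. It more naturally means the measure already chosen by the investigators.
- The three effects of the repeated measures ANOVA might be counted as extra chances of success. The section is about change, for which the group-by-time interaction is the relevant test, and nothing says that a group or time main effect would count.
- Doubts about the 34 per group might be used to add weight here. They belong to a different point.

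**Conclusion.** The point holds conditionally. The article names two primary outcomes in two places, refers to one in two others, sizes one, and tests at 0.05 without a success rule. If either outcome can carry the trial, the familywise false positive rate is about 7% to 9.75% for correlations from 0.9 down to 0, against a nominal 5%. This assumes two-sided tests at 0.05, no effect on either outcome and approximately normal test statistics. If both are required, the error is controlled but power is limited by the weaker test, and the article makes no power statement for Timed Up and Go.

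This should be fixed but does not undermine the design: both outcomes are prespecified, there are only two, the sized one can be identified, and the inflation cannot exceed 10% in total.

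**What to change.** Reconcile the Abstract, Primary outcome measure, Statistical analysis and Sample size sections by stating one rule before results are seen:

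- Test Step Quick Turn sway first, through the group-by-time effect at 16 weeks, at two-sided 0.05. This is the outcome closest to the trial's aim and the one that was sized.
- Test single-task Timed Up and Go at two-sided 0.05 only if sway is significant. Naming the single-task version also settles which form is meant.
- Use the same count of primary outcomes, and the same order, in all four sections.

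**Cost.** No extra participants and no change to the level used for sizing. Timed Up and Go loses its stand-alone confirmatory claim if sway is not significant. The protocol needs a short amendment and the registration must be aligned with it.

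**Alternatives.** Holm's procedure, or an explicit rule that both outcomes must be significant, would also control the error and keep both as primaries. Each costs some power: Holm because the smaller p-value must meet 0.025, the both-required rule because power is capped by the weaker outcome. If both are required, a power statement for Timed Up and Go should be added.
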